The DAFNE approach to diabetes care delivery was greeted with considerable enthusiasm by patients [10], healthcare professionals [11] and policy makers [12]. Since publication of the results of the DAFNE trial a further 74 diabetes teams in the UK and Ireland have undertaken training of their staff to deliver the programme [8]. Preliminary reports of audit data from a number of these DAFNE centres suggest that improvements in glycaemic control and psychosocial measures of wellbeing similar to the DAFNE trial are being achieved in routine practice [13]. However, unlike the situation in Germany where sustained benefit has been reported [7], long-term data from the UK indicate a diminution of the HbA_1c _improvement [14]. This raises the issue of how best to support the long-term needs of a patient who has been through DAFNE training. This is the central question being addressed in the Irish DAFNE Study. The hypothesis on which the study is based is that group follow-up of DAFNE graduates is superior to individual follow-up. The philosophy of the DAFNE programme is grounded in Therapeutic Patient Education Theory [15]. The group education approach incorporating theories of adult learning has been used in structured education programmes for people with Type 2 diabetes, such as DESMOND [16] and ROMEO [17]. This paper describes the design, setting, interventions and outcomes of the Irish DAFNE Study, an 18 month cluster randomised trial of self-management support among patients with Type 1 diabetes.

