### DAFNE and Study Interventions

The DAFNE course is delivered over 5 consecutive days and involves 38 hours of structured education in all aspects of managing Type 1 diabetes. The education is delivered by a Diabetes Specialist Nurse, Dietitian and Doctor all of whom have undergone training in delivery of the DAFNE curriculum. Figure 2 illustrates the rigorous training process that a diabetes team has to go through to become a DAFNE centre. One of the real strengths of the DAFNE programme is the quality assurance that is incorporated into its delivery. DAFNE educators regularly undergo peer review (both within their centre and via external peer review) to ensure they are maintaining a consistent high standard of course delivery. This means that the basic package (the DAFNE course) delivered in each of the participating DAFNE centres was uniform and standardised to a level appropriate for a research study. Details of the individual sessions that comprise the DAFNE course are available on the DAFNE Collaborative website [8] and all resource literature is available to DAFNE graduates via the DAFNE Online website [19]. Participants in the intervention arm centres also receive sessions on goal setting and action planning as part of the DAFNE week.

Following DAFNE course delivery patients are invited back as a group for a 6 week return visit with the educators (nurse and dietitian) who delivered their original course. This was considered an essential component of the basic DAFNE course and was not removed from either arm of the study. After this 6 week return visit participants in the usual care arm of the study are offered return visits to the diabetes clinic at 6, 12 and 18 months post DAFNE training. This reflects usual care in Irish DAFNE centres prior to the study. The protocol does not stipulate what issues are covered in these visits. The only stipulation is that participants should not be seen in a group setting. It is recognised that attempts are likely to be made to have patients in this arm of the study seen by the doctor, nurse and/or dietitian involved in their original DAFNE training. However, patients may also be seen by diabetes team members not trained in DAFNE.

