Participants in the intervention arm of the study are also seen at 6, 12 and 18 months. The 6 and 12 month visits are organised as group education sessions and build on the concepts of goal setting and action planning introduced during the original DAFNE course. A follow-up curriculum was developed to guide DAFNE educators involved in delivering these sessions and specific training in the delivery of this curriculum was given to all intervention arm DAFNE educators. Groups are encouraged to determine their own priorities and select from a range of DAFNE self-management skills review topics designed specifically for these follow-up sessions. The role of the DAFNE educator is to achieve a blend of a patient-centred and curriculum-centred approach to the session. Follow-up curriculum topics include HbA_1c _and targets, diary keeping and self-monitoring, principles of dose adjustment, carbohydrate calculation, hypoglycaemic management, exercise and physical activity, alcohol and sick day rules. An example of a typical timetable for a group follow-up session is outlined in Table 1. Where DAFNE graduates are unwilling or unable to participate in a follow-up session with their original group they are offered a follow-up session with a different DAFNE group from that centre. Every effort is made to avoid delivering follow-up on a one-to-one basis in this arm of the study. In keeping with an emphasis on quality assurance an external peer review of the delivery of one 6 month follow-up session in each of the 3 intervention arm centres will be undertaken during the study.

**Table 1 T1:** Typical timetable used during the intervention follow-up sessions

09:30	Welcome
09:40	HbA_1c _results, review of blood sugar and targets

10:10	Quiz to identify 3 areas the group would like to focus on (patient-centred approach)

10:20	Curriculum used to guide group-led discussion of identified topics

12:10	Goal setting and action planning

12:30	Close

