### Statistical Considerations

#### Sample Size

We used a sample size calculator designed for cluster randomised trials [25]. We based the sample size calculation on an anticipated HbA_1c _difference between the 2 arms of the study of 0.5 percent from month 6 onwards. This came from the observation in the UK study that DAFNE training led to a 1.0 percent drop in HbA_1c _at 6 months but reverted to 0.5 percent by 12 months [9]. Our study hypothesis is that group follow-up will be able to maintain the benefit out to 18 months. Unlike the UK DAFNE Study patients were not excluded with baseline HbA_1c _below 7.5 percent. Based on a standard deviation of HbA_1c _of 1.2 and an intra-class correlation co-efficient of 0.05 we estimated that 450 patients would be required to detect a 0.5 percent difference with 90 percent power.

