#### Planned Analyses

Initially, descriptive analysis will be conducted to fully profile both the study centres (number of educators and doctors, years since initial training and size of DAFNE waiting list) and the participants (age, gender, years since diagnosis, baseline HbA_1c_, weight, lipid levels and socio-economic status). The main analysis, for the entire cohort, will be an intention-to-treat analysis and will compare differences between HbA_1c _at baseline and at 18 months in the 2 treatment arms, adjusting for age, gender, study centre and years since diagnosis. Changes in the rate of severe hypoglycaemia will also be examined.

In addition to this intention-to-treat analysis we will also undertake a "per protocol" analysis on those individuals who attended all of the educational sessions in the intervention arm.

Sensitivity analyses will explore whether adherence to the intervention influences the effect of the intervention on primary outcome.

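### The supplementary per-protocol analysis applies an attendance rule to the intervention arm only, so it either has no comparator or is likely biased towards group follow-up

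*Protocol article*

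**What the plan says.** All references are to the protocol article.

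- **Planned Analyses**, primary comparison: "The main analysis, for the entire cohort, will be an intention-to-treat analysis". It compares HbA1c at baseline and 18 months between arms, adjusted for age, gender, study centre and years since diagnosis.
- **Planned Analyses**, supplementary: a per-protocol "analysis on those individuals who attended all of the educational sessions in the intervention arm". No comparison group is named and no criterion is given for usual care. The section also mentions sensitivity analyses on adherence.
- **DAFNE and Study Interventions**, usual care: after the 6-week return visit, participants are "offered return visits to the diabetes clinic at 6, 12 and 18 months post DAFNE training".
- **DAFNE and Study Interventions**, intervention: participants are also seen at 6, 12 and 18 months. "The 6 and 12 month visits are organised as group education sessions". The section foresees non-attendance: "Where DAFNE graduates are unwilling or unable to participate in a follow-up session with their original group", another group's session in the same centre is offered.
- **Background**: the hypothesis is that "group follow-up of DAFNE graduates is superior to individual follow-up".

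**The concern.** Attendance at every session happens after randomisation and depends partly on the participant. People who come to everything may be more engaged with self-management and so improve more whichever follow-up their centre was allocated. Filtering one arm on this behaviour and not the other mixes any effect of group follow-up with a difference in the kind of patient compared. The adjustment variables are stated for the main analysis, and none of them measures engagement.

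The expected direction is the one the trial hopes to show. If the intention-to-treat result were null, a benefit among those who attended could be reported when selection alone had produced it.

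The set itself is also unclear. The wording does not say whether the DAFNE week and 6-week visit, which both arms receive, count as educational sessions, or only the 6- and 12-month group sessions.

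**Working it through.** The article gives no figure for attendance or for the size of the per-protocol set, so there is nothing of its own to reproduce here. The check has two parts.

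**1. What the sentence permits**

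| Reading | Intervention arm | Usual-care arm | Result |
|---|---|---|---|
| Literal | Full attenders | None named | No between-arm effect |
| Inferred | Full attenders | All controls | Selected against unselected on attendance |

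Neither gives a sound between-arm comparison. A parallel criterion was available, since usual care also has visits scheduled at 6, 12 and 18 months.

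**2. Size of the bias under the inferred reading**

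Inputs:
- Target difference: 0.5 percentage points (Sample Size).
- Outcome: change in HbA1c from baseline to 18 months (Outcomes and Measurement).
- p, the share of participants who would attend everything: not in the documents; assumed 0.5 to 0.9.
- g, the amount by which the mean fall in HbA1c among would-be full attenders exceeds that of the rest, under the same follow-up: not in the documents; assumed 0.2 to 0.5.

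Because the outcome is change, g must be a gap in change. A difference in HbA1c level already present at baseline and unchanged at 18 months cancels.

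Set the true effect to zero. Let a be the mean fall in would-be full attenders and b the mean fall in the rest, so g = a − b. By randomisation the control arm is expected to have the same mix:

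- Full attenders in the intervention arm: a
- All controls: p × a + (1 − p) × b
- Difference: a − p × a − (1 − p) × b = (1 − p) × g

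| p | g = 0.2 | g = 0.3 | g = 0.5 |
|---|---|---|---|
| 0.9 | 0.02 | 0.03 | 0.05 |
| 0.7 | 0.06 | 0.09 | 0.15 |
| 0.5 | 0.10 | 0.15 | 0.25 |

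Against the target: 0.02 / 0.5 = 4% and 0.25 / 0.5 = 50%.

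**3. What a selection rule for controls would do**

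Let π be the share of would-be full attenders among the controls analysed, with the mean fall in the remaining controls still b. The bias becomes (1 − π) × g.

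- No rule for controls: π = p, as tabulated.
- Only controls with an 18-month value: if a share r of controls has one and includes all would-be full attenders, π = p / r. This exceeds p when r is below 1, so the bias is smaller.
- A comparable attendance rule: π moves towards 1. The bias vanishes only if attendance selects the same kind of patient in both arms.

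**The case against.** **The comparator is inferred, and detail may sit in a fuller document.** It is true that the sentence names no comparator. But the article does fix the selection rule, and fixes it for one arm. Followed as written, it yields one of the two readings above, so this is more than detail left out.

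**Controls may not be wholly unselected.** This stands. The outcome needs an 18-month value, so unless missing values are imputed, controls are partly selected too and (1 − p) × g overstates the bias.

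**The direction is not proven.** This also stands. A reader might infer that the analysis is certainly biased towards group follow-up. The article has no attendance or outcome data, and if full attenders improved less than others, the sign would reverse. Likely is as far as the text goes.

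**The bias is modest beside sampling error.** With the article's SD of 1.2, ICC of 0.05 and clusters of about 75, the design effect is 1 + 74 × 0.05 = 4.7. With 225 per arm the standard error is 1.2 × √(2 × 4.7 / 225) ≈ 0.245. At p = 0.7 and g = 0.3 to 0.5, a bias of 0.09 to 0.15 is about 0.4 to 0.6 standard errors. That is a fair sense of scale, but the bias would remain however precise the estimate.

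**The adherence sensitivity analysis.** A reader might infer that it shares the flaw. The article says only: "Sensitivity analyses will explore whether adherence to the intervention influences the effect of the intervention on primary outcome". It gives no method, and a sound method would fit that sentence, so the documents do not support calling it flawed.

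**The analysis is supplementary.** This is correct and limits the severity.

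**Conclusion.** The point holds for the per-protocol analysis. Its population is defined by post-randomisation attendance in one arm, so it either lacks a comparator or likely favours group follow-up.

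Under a true null, the bias is about 0.02 to 0.25 percentage points, or 4% to 50% of the 0.5 target. This rests on assumed values (p = 0.5 to 0.9, g = 0.2 to 0.5), on full attenders improving more under either follow-up, and on all controls being analysed. It is smaller if controls without an 18-month value drop out.

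Severity is low to moderate. A reader might infer that the trial's main conclusion is at risk; it is not, because intention-to-treat on the entire cohort is the main analysis and is untouched by this rule.

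**What to change.** Reword the per-protocol paragraph to:

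1. name the comparator and state which sessions count;
2. apply a comparable attendance rule in both arms, for example attendance at the scheduled 6-, 12- and 18-month visits;
3. adjust for baseline HbA1c;
4. label the result exploratory and subordinate to the intention-to-treat analysis.

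The change needs no new outcome data, but it does need visit attendance for both arms. The article does not say that attendance is recorded; its measurement schedule (Table 2) has data collected at those three times, which may serve as a proxy.

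The cost is a smaller analysis set. Selection bias is reduced but not necessarily removed: a clinic visit and a three-hour group session may attract different patients, and a control who misses an offered visit has not clearly departed from protocol.

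A complier-average causal effect estimate, with centre allocation as the instrument and allowance for clustering, could be at most an additional analysis. Dividing the intention-to-treat effect by the share attending everything assumes that allocation does nothing for anyone else. That is doubtful here: intervention centres also deliver goal-setting and action-planning sessions within the DAFNE week, and someone who attends one of the two group sessions is partly treated. Any benefit from these would be credited to full attenders and would inflate the estimate.

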#### Sub-group analyses

For those individuals with HbA_1c _above and below 7.5 percent at baseline a separate intention-to-treat analysis will be conducted to compare differences between HbA_1c _at baseline and at 18 months in the 2 treatment arms. Changes in the rate of severe hypoglycaemia will also be examined for those with baseline HbA_1c _above and below 7.5 percent at baseline. The rationale for this approach is that "benefit" from DAFNE training for individuals with low HbA_1c _may amount to a reduction in the frequency of severe hypoglycaemia.

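### Dependence of benefit on baseline HbA1c is examined by separate analyses above and below 7.5%, with no arm-by-baseline comparison, so a result significant in one stratum only could be misread as a differential effect

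*Protocol article*

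**What the plan says.** The section Sub-group analyses splits the cohort by baseline HbA1c, "above and below 7.5 percent at baseline", and says that "a separate intention-to-treat analysis will be conducted" to compare the change in HbA1c to 18 months between the arms. It adds a second outcome for the same strata: "Changes in the rate of severe hypoglycaemia will also be examined for those with baseline HbA_1c _above and below 7.5 percent at baseline". The reason given is that benefit from DAFNE training in people with low HbA1c "may amount to a reduction in the frequency of severe hypoglycaemia".

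Both strata will be populated. The Sample Size section notes that, unlike in the UK trial, "patients were not excluded with baseline HbA_1c _below 7.5 percent". The article nowhere mentions an interaction term or any other comparison of the arm effect between strata. Planned Analyses specifies the main whole-cohort comparison, which this point does not touch.

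**The concern.** The rationale implies that what a patient gains depends on where baseline HbA1c lies. That is a question of effect modification, and it is answered by estimating the difference between the two stratum effects. Two within-stratum comparisons do not estimate that difference. Each asks only whether the effect in its own stratum is distinguishable from zero, and the answer depends heavily on stratum size.

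If one stratum is significant and the other is not, the natural reading is that group follow-up works only above, or only below, 7.5%. That pattern can easily arise when the true effect is the same in both. The Discussion says that the results should inform future policy on diabetes education in Ireland, so a spurious restriction to one stratum would matter. The same applies to severe hypoglycaemia, where the rationale expects the low stratum to differ.

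**Working it through.** The sub-group section gives no figure of its own to reproduce, so the check asks how often the separate analyses would disagree when the strata do not truly differ.

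**Inputs from the protocol.** Effect 0.5, SD 1.2 and ICC 0.05 (Sample Size); six centres of about 75 (Randomisation and Patient Recruitment); three intervention centres (DAFNE and Study Interventions), so three per arm and 225 patients per arm.

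**Assumptions.** The share f of patients below 7.5% is not given and is varied from 10% to 50%. Tests are two-sided at 5% with a normal approximation. Both strata in a centre share the same centre effect, and the analysis accounts for clustering.

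**Variance of the arm difference in a stratum holding a share x of patients**

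- Centre part, common to both strata: 2 × 0.05 × 1.44 / 3 = 0.048
- Patient part: 2 × 0.95 × 1.44 / (225x) = 2.736 / (225x)

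**Worked case, f = 25%**

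- Low stratum: 2.736 / 56.25 = 0.0486; total 0.0966; SE 0.311; power Φ(0.5/0.311 − 1.96) = 36%
- High stratum: 2.736 / 168.75 = 0.0162; total 0.0642; SE 0.253; power 51% (0.505)
- Correlation of the two estimates: 0.048 / √(0.0966 × 0.0642) = 0.61
- Probability that both are significant (bivariate normal): 0.28
- Probability that exactly one is significant: 0.363 + 0.505 − 2 × 0.280 = 0.31

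**Over the range of f, with an identical true effect of 0.5 in both strata**

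| Share below 7.5% | Power, low | Power, high | Correlation | Exactly one significant |
|---|---|---|---|---|
| 10% | 23% | 52% | 0.47 | 40% |
| 20% | 33% | 51% | 0.58 | 33% |
| 25% | 36% | 51% | 0.61 | 31% |
| 30% | 39% | 50% | 0.63 | 29% |
| 40% | 43% | 48% | 0.66 | 27% |
| 50% | 46% | 46% | 0.66 | 27% |

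A valid test of the interaction would signal a difference in 5% of such trials.

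**What the interaction can deliver.** The shared centre effect cancels in the difference between strata, so its SE is √[2.736/225 × (1/f + 1/(1−f))], provided that the arm contrast between strata does not itself vary by centre. At f = 25% this is √(0.0486 + 0.0162) = 0.255. Power for an interaction of 0.5 points is Φ(0.5/SE − 1.96): 44% at f = 20% (SE 0.276), 50% at 25% and 62% at 50% (SE 0.221).

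**The boundary.** Suppose that values are reported to one decimal and that baseline HbA1c is normal with SD 1.2. The share recorded as exactly 7.5 is then Φ((7.55 − μ)/1.2) − Φ((7.45 − μ)/1.2). For an assumed mean of 8.0 this is 3.05%, or 13.7 of 450. For 8.6 it is 2.18%, or 9.8 of 450. So about 10 to 14 patients would be in neither stratum as worded.

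**The case against.** The strongest reply is that this is a short section of a journal article. Stratum-specific comparisons are compatible with an interaction test that a separate analysis plan might add. That plan is not shown, so it cannot be said that no such test will ever be done. What stands is that the article names a method, and that method does not answer the question its own rationale raises.

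A reader might infer that the plan will declare group follow-up effective in one stratum only. The article does not support that: it gives no significance rule for sub-groups and no rule for comparing them, and hypoglycaemia is only to be examined. The risk is of a misreading that the plan leaves open.

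The rationale can also be read more narrowly. Both arms receive DAFNE training, so the sentence may only explain why hypoglycaemia is a relevant outcome at low HbA1c. That reading is possible, but analysing HbA1c and hypoglycaemia on both sides of the cut still invites a comparison between strata.

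Two stronger numerical readings fail. Discordance of about one half follows only if the stratum estimates are independent, and they are not, because they come from the same centres. Nor is the interaction generally better estimated than the stratum effects. At a 25% share its SE of 0.255 is below the low-stratum 0.311 but no better than the high-stratum 0.253. It also relies on there being no centre-by-stratum variation; if that is allowed for, the contrast is again between three and three centres.

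Finally, wording a cut-point as above and below is common shorthand, and the gap at 7.5% is small.

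**Conclusion.** The point holds as a recommendation on a secondary analysis; the primary comparison is unaffected. Separate stratum analyses cannot show whether benefit depends on baseline HbA1c. With an identical true effect of 0.5, they would leave exactly one stratum significant about 27-40% of the time for shares below 7.5% of 50% down to 10% (about 31% at a 25% share), against 5% for a valid interaction test. These figures rest on the protocol's SD, ICC, effect and centre sizes, on the assumed share, and on a normal approximation with shared centre effects.

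The interaction test has its own limit: power is only about 44-62% for a 0.5-point difference at shares of 20-50%, so a null interaction would not show that the effects are equal. That supports cautious reporting of the interaction and does not make the separate tests adequate. The unassigned value of exactly 7.5% is minor.

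**What to change.** - Fit one model to the whole cohort with an arm × baseline-HbA1c interaction that respects centre clustering and allows for centre-by-baseline variation where it can be estimated.
- Fit a parallel count model for severe hypoglycaemia with the same interaction.
- Base any claim of a sub-group difference on the interaction estimate and its confidence interval. Report the stratum estimates with confidence intervals as descriptive.
- State in advance that the interaction has limited power and that a null result does not show equal effects.
- Define the strata as <7.5 and >=7.5.

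This changes analysis wording only. All the data needed are already in the measurement plan (Table 2), so there is no cost in patients, visits or assays.
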